## Results

Recruitment to the study began June 17, 2016 and ended September 14, 2016. Data were collected using direct entry of online surveys tools (Qualtrics [45], Articulate Online [49]) by February 2017, and are currently undergoing analyses. The CONSORT diagram (Figure 5) presents the flow of participants during recruitment, enrollment, and participation. Of the 398 individuals who expressed interest in participating, 91 were determined to be eligible through the screening process. A total of 60 individuals returned their informed consent and were randomized, of whom 59 individuals were intended-to-treat. A total of 50 participants in the study were retained through the 16-week enrollment.

## Discussion

The primary aim of this trial is to preliminarily evaluate an Internet-delivered DBT skills training intervention for suicidal and heavy episodic drinkers. Research on suicidal individuals who engage in HED is paramount to understanding and managing suicide risk, particularly as it pertains to high-risk populations who are less inclined to seek formal treatment. The set of protocols used in DBT to manage acute and chronic suicidality was translated relatively seamlessly for use in this pilot study’s Web-based approach, demonstrating their potential utility as tools for remote risk-management in computerized interventions. A concern of this treatment is the 8-week waiting period; however, waiting times are often a reality for individuals seeking assessment and treatment (eg, mean=65.4 days) [56] due to resource or staff shortages [57-60], and we believe we can answer an important question about placing high risk individuals on waiting lists. Participants were fully informed about the possibility of being randomized to an 8-week waiting list, as well as their rights to withdraw from the study at any time. Referrals to treatment and crisis services were provided whenever participation was declined or withdrawn.

One major aim of the study was to investigate the feasibility of recruiting and retaining participants from this population. Sixty eligible individuals were recruited within three months, demonstrating the feasibility and effectiveness of the online recruitment strategy. Retention rates, particularly for waitlisted participants, were anticipated as a potential challenge, with findings in the literature suggesting an association between longer wait periods and reduced treatment motivation and retention [61,62]. To address this problem, customized reminders were sent to all participants to encourage treatment engagement and assessment completion [63]. Finally, 83.3% (50/60) of all participants were retained in the study by the end of their enrollment, suggesting that customized reminders may be an effective strategy to mitigate study dropout rates.

The level of risk commonly attributed to such studies may be inhibitive to research. Nevertheless, grounds for the safeguarding of participant safety can be established with careful implementation of validated risk-management protocols, which equip researchers with contingencies against anticipated harm in conducting much-needed studies. In addition, the feasibility of recruiting, retaining, and monitoring participants demonstrated in this pilot study provides preliminary suggestions for the developing field of research on technologically-assisted interventions that may become beneficial alternatives to traditional therapy, or mediate adaptive help-seeking in at-risk and underserved populations.

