To address this treatment gap, an Internet-delivered DBT skills intervention targeting the underlying mechanism of emotion dysregulation was adapted for individuals who endorse suicidal thoughts and engage in HED. The current pilot study is a proof of concept study that seeks to evaluate the feasibility, acceptability, and preliminary efficacy of a DBT skills training intervention delivered via technology (ie, Web-based portal). The following aims are: (1) to determine the feasibility of recruiting clients, administering the treatment, and retaining clients in the treatment; (2) to evaluate the safety of the treatment with respect to potential adverse events; (3) to assess the feasibility of the research methodology (eg, reliability of the measures used, feasibility of random assignment to treatment, appropriateness of the control condition); and (4) to evaluate the feasibility of using a wait-list control group in this line of research, and changes over time among individuals in such a comparison group.

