### Procedure

Semistructured phone screening interviews were conducted with individuals who initiated contact via phone or email and remained interested after receiving information about the study. Phone screens were either prescheduled or conducted during the first call of contact, depending on caller preference, and were administered by trained research assistants. Eligible individuals received informed consent forms to sign and return, and were randomized once their signed forms were received at the study site.

Following randomization into the immediate-treatment and waitlist groups, participants in both conditions received a baseline assessment, followed by identical monthly assessments in the ensuing four months. Primary monthly outcomes included suicide ideation (Scale for Suicidal Ideation [33]), severity and frequency of alcohol consumption (Alcohol Use Disorders Identification Test; AUDIT [34], and Self-Administered Web-Based Timeline Followback [35,36]), and emotion dysregulation (Difficulties in Emotion Regulation Scale [37]). Secondary outcome measures included the Reasons for Living Inventory [38], Short Inventory of (Alcohol) Problems (SIP) [39], Patient Health Questionnaire [40], and Dialectical Behavior Therapy - Ways of Coping Checklist [41]. All participants also received brief online weekly assessments on suicide ideation and alcohol consumption. Suicide risk was monitored via weekly assessments.

Prior to treatment, participants also responded to their expectancy of outcome along with the credibility of the intervention (Credibility/Expectancies Questionnaire [42]). At the end of the treatment period, participants reported on their treatment satisfaction (Client Satisfaction Inventory-Short Form [43]) and therapeutic alliance (California Psychotherapeutic Alliance Scale [44]). Participants actively receiving treatment also received brief daily surveys about their urges to quit treatment, use of DBT skills, and engagement level.

All assessments were administered through an online survey platform (Qualtrics [45]) made accessible to participants via Uniform Resource Locator links in scripted emails sent at scheduled timepoints. As compensation for their participation, participants received up to US $120 in Amazon gift cards upon completing each monthly survey (baseline=$15, 4-week=$20, 8-week=$25, 12-week=$30, and 16-week=$30).

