### Intervention

One primary aim of iDBT-ST is to replace maladaptive behavioral strategies with alternative strategies for coping and emotion regulation. The current intervention comprises the skill-training component alone, which is administered in a computerized format. The intervention was modified from an online DBT skills training intervention for emotion dysregulation [48].

Participants randomized into the iDBT-ST group were immediately enrolled into the online treatment program, and received weekly sessions over a period of 8 weeks. After completing the eighth session, participants in active treatment were transitioned into a follow-up phase that entailed monthly and weekly assessments without treatment. Participants randomized into the waitlist group received repeated monthly assessments as well as weekly surveys for 8 weeks prior to receiving treatment.

The iDBT-ST intervention was administered through an online electronic learning server (Articulate Online [49]) which consists of 8 sessions (Table 1) accessible through an access portal individualized for each participant, with one new session activated each week. The sessions begin with a weekly assessment, followed by (1) a review of the last session at weeks 2-8, (2) an introduction of the current session, (3) skills teaching, and (4) summary and consolidation. The skills were taught via videos and graphics describing the skills and examples, along with interactive activities. The intervention completion rate of each participant was also monitored through the server. If consented by participants, reminders to complete sessions were sent via their preferred method before the next session became available. Individualized assignments of skill practice were provided following the completion of each session. See Figure 1, Figure 2, and Figure 3 for screenshots of the intervention.

**Table 1 table1:** Description and function of session contents.

Session	DBT module	Skills	Function
1	Mindfulness	Observing, Describing, Participating	To introduce the foundational skills to develop nonjudgmental awareness of the present
2	Mindfulness	Nonjudgmentally, One-Mindfully, Effectively	To teach how to practice mindfulness with skillful effectiveness
3	Addiction	Dialectical Drinking, Clear Mind	To help learners find a middle path between oppressive sobriety and unrestrained freedom of drinking, and develop a clear mind

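### The Discussion uses one pooled retention figure to suggest that reminders reduce dropout; the design cannot estimate a reminder effect, and the pooled figure does not address waitlist retention

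*Protocol article*

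**What the plan says.** The relevant statements are all in the protocol article.

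- **The worry (Discussion).** "Retention rates, particularly for waitlisted participants, were anticipated as a potential challenge". The fourth aim in the Introduction is in part "to evaluate the feasibility of using a wait-list control group in this line of research".
- **The response (Discussion).** To meet that worry, "customized reminders were sent to all participants to encourage treatment engagement and assessment completion".
- **The result (Discussion).** "83.3% (50/60) of all participants were retained in the study by the end of their enrollment". The Results and Abstract give the same 50, also without a split by arm.
- **The inference (Discussion).** The result is read as "suggesting that customized reminders may be an effective strategy to mitigate study dropout rates".
- **What was randomised (Methods, opening paragraph).** Immediate start of the 8-week programme or a start after 8 weeks of waiting. Reminders and payments were not randomised.
- **What else ran alongside.** Under Procedure, "participants received up to US $120 in Amazon gift cards upon completing each monthly survey", on the schedule "baseline=$15, 4-week=$20, 8-week=$25, 12-week=$30, and 16-week=$30". Under Managing Risk, all participants were sent weekly risk questionnaires, and certain ratings led to a phone call, or an email if the call was not answered.

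**The concern.** There are two faults in the same short argument.

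First, a retention rate in a group that all received reminders is offered as evidence that reminders work. That needs a comparison: people without reminders, or at least a benchmark rate from a similar study. The article gives neither. It cites literature linking longer waits to poorer retention but quotes no rate. Payments and weekly contact are equally plausible reasons for people to stay, and the sentence mentions neither.

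Second, the question posed is whether waitlisted people stay, and the answer is a rate over both arms at the end of 16 weeks. A pooled rate can look satisfactory while one arm does poorly. Week 16 is also late for this purpose, because the wait ends at week 8.

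At stake is what the pilot passes on. Its declared purpose is feasibility and the design of a full-scale trial. A reader planning that trial could take from this paragraph that reminders are a tested retention strategy and that a waitlist control retains well. The paragraph as argued establishes neither.

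**Working it through.** **Inputs.** Randomised: 31 immediate, 29 waitlist, 60 in total (Participants; Randomization). Retained at 16 weeks: 50 (Results; Discussion). One immediate-arm participant completed no assessments (Participants). Payments: $15, $20, $25, $30, $30 (Procedure).

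**Step 1: reproduce the stated figure.** 50/60 = 0.8333, or 83.3%. This agrees with the Discussion. The exact (Clopper-Pearson) 95% interval takes the 2.5% quantile of Beta(50, 11) and the 97.5% quantile of Beta(51, 10), giving 71.5% to 91.7%.

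**Step 2: look for a reminder contrast.** An effect of reminders is retention with reminders minus retention without them. The Discussion says reminders went to all, so the first term is 83.3% and the second is not observed. The randomised contrast, immediate against delayed start, is not a reminder contrast. The effect cannot be estimated from this design at any sample size.

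**Step 3: list the concurrent causes.** Payments sum to 15 + 20 + 25 + 30 + 30 = $120. They rise up to week 12 and are level at the last step. Weekly risk questionnaires with follow-up contact also went to both arms. Reminders, payments and contact are fully confounded.

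**Step 4: see what the pooled figure says about the waitlist arm.** Not retained: 60 − 50 = 10. Assume that the participant with no assessments is one of the ten. Then one loss lies in the immediate arm and nine are unallocated in the visible text. If *w* of the nine are waitlist losses, waitlist retention is (29 − *w*)/29 and immediate retention is (31 − (10 − *w*))/31.

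| *w* | Waitlist | Immediate | Immediate minus waitlist |
|---|---|---|---|
| 0 | 29/29 = 100% | 21/31 = 67.7% | −32.3 points |
| 5 | 24/29 = 82.8% | 26/31 = 83.9% | +1.1 points |
| 9 | 20/29 = 69.0% | 30/31 = 96.8% | +27.8 points |

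Every row gives the same 50/60. The table shows only that the pooled figure does not determine waitlist retention. It does not estimate either arm.

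**Step 5: check the time point.** The waitlist arm waits during weeks 0 to 8 and is treated during weeks 8 to 16 (Intervention; Analyses). The immediate arm is treated first and then followed up. Week-16 retention therefore mixes waiting and treatment in one arm, and treatment and follow-up in the other. Whether people stay through the wait is answered at week 8, for which the visible text gives no retention figure.

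**The case against.** The strongest reply is that this is a doubly hedged remark in a Discussion. The authors write of a suggestion and of what may be, the arithmetic is right, the denominator is all 60 randomised, and no outcome, model or planned analysis depends on the sentence. That stands as to weight: this is an unsupported suggestion, not a firm causal claim. It does not rescue the inference, because the retention rate is still offered as evidence for reminders and the design supplies none.

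The second reply is that the flow diagram (Figure 5) probably holds retention by arm. It is not reproduced in the text at hand, so nobody should conclude that the split was never reported, or that the range in the table above describes what the article leaves open. What stands is narrower: the Discussion argues from the pooled number alone. The reminder fault remains whatever the figure shows.

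Three stronger readings might tempt a reader, and the documents do not support them.

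- *That the article contradicts itself on who received reminders.* The Intervention section says "If consented by participants, reminders to complete sessions were sent via their preferred method before the next session became available", while the Discussion speaks of all participants. The first concerns treatment sessions; the second is broader and includes assessments. Both can be true, for example if everyone had assessment reminders and those who agreed also had session reminders. Any subgroup without session reminders would be self-selected and no valid comparison.
- *That the Abstract uses a different denominator.* It lists 60, 59 and 50 but gives no percentage and does not tie the 50 to the 59.
- *That 83.3% is passed off as retention in treatment.* The Discussion labels it retention in the study. Session completion was monitored through the server and may properly be reported with the trial results.

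**Conclusion.** The point holds, in limited form. The 83.3% (50/60; exact 95% CI 71.5% to 91.7%) is correct as a description of overall study retention. It gives no support to the suggestion about reminders, because nobody was assigned to go without them and payments and weekly contact ran alongside. Nor does it by itself answer the waitlist-retention question that the same paragraph raises: the pooled figure is compatible with waitlist retention anywhere from 69.0% to 100%, and week 16 is not the end of the wait.

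The first conclusion rests on the article's own statements about who got reminders and what was randomised. The range in the second assumes that the participant with no assessments is among the ten not retained, and it would collapse to a single value if Figure 5 gives the split. The planned efficacy analyses are unaffected. What changes is what the pilot can claim about its retention strategy and its control condition.

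**What to change.** 1. Delete the sentence part that links retention to reminders. Alternatively, replace it with a statement that reminders, payments and weekly contact were given together and that their contributions cannot be separated in this design.
2. Base the waitlist-feasibility conclusion on retention by randomised arm, with denominators 31 and 29, at week 8 (end of the wait) and week 16, each with an exact 95% interval. If Figure 5 already gives the counts, cite them in the Discussion.
3. Keep the pooled 83.3% as a description of overall study retention.

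The cost is a short text edit and a four-cell table from data already held; no new data or analysis model is needed. The price is a less favourable claim, with wider intervals for each arm than for the pooled figure.

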## Appendix

Multimedia Appendix 1 Informed consent.

Multimedia Appendix 2 Caring email sent to those unreachable by phone.

## Abbreviations

AUDIT: Alcohol Use Disorders Identification Test
DBT: dialectical behavior therapy
GEE: generalized estimating equation
HED: heavy episodic drinking
HLM: hierarchical linear modeling
iDBT-ST: Internet-delivered Dialectical Behavioral Therapy Skills Training
NIAAA: National Institute on Alcohol Abuse and Alcoholism
RCT: randomized controlled trial
UWRAP: University of Washington Risk Assessment Protocol
